### Procedures, participants, and analyses

#### Recruitment and screening

The subjects of this study will be identified from local HPN databases of the different study sites. Patients will be selected by the attending physicians and local nurse practitioners. The local investigator will provide information about the study by phone and will subsequently send information material, including the Informed Consent Agreement, to the patient’s home address. Informed consent will be obtained before the start of any study-specific procedures (e.g., randomization). Data will be saved in a documentation system based on electronic Case Report Forms (eCRFs; CastorEDC 2017.9). CastorEDC is compliant with ICH-GCP and all the regulations required by FDA 21CFR Part 11 for electronic data management.

#### Randomization

Randomization will be performed centrally by the principal investigators using an online randomization module (CASTOR EDC 2017.9) in a 1:1 ratio to either a SD group or a CS group (Figs. 2 and 3). Randomization will be stratified by country to balance differences in national treatment guidelines and different antimicrobial susceptibility patterns. Variable block randomization consisting of two, three, or four marbles will be used to provide treatment allocation in equal proportions. We considered a blinded design, but the treatment strategy protocols of both groups differ to such an extent that this precludes adequate blinding. Besides this, an unblinded (more pragmatic) design fits best with the current ideas about the external validity of cost-effectiveness studies.

#### Baseline examination

At the start of the trial, patient characteristics (from existing electronic patient system, medical history, and/or by physical examination), results of earlier obtained culture swabs, and/or blood results will be collected on the eCRF by the investigator.

#### Choice of antibiotic drug(s)

Patients will be treated according to the respective marketing authorizations and national MRSA guidelines as previously mentioned (Table 2). The choice of antibiotic drugs depends on known allergies, expected decreased absorption in the case of short bowel, and susceptibility patterns of the *S. aureus* isolates. If during the course of the study the treating physician or consulted specialist infectious diseases feels that a particular antibiotic drug is clearly indicated or contra-indicated in a patient, the choice of the antibiotic drug may be changed at his/her discretion.

**Table 2 Tab2:** Systemic combination therapy for eradication of MRSA carriage in complicated carriage according to the Dutch MRSA guideline [10]

Dutch MRSA guideline	Antibiotic 1	Antibiotic 2
Recommended	Sulfamethoxazole/Trimethoprim 960 mg twice daily *or* Doxycycline 200 mg once daily	Rifampicin 600 mg twice daily
Alternative^ɑ^	Clindamycin 600 mg thrice daily *or* Clarithromycin (or another macrolide) 500 mg twice daily *or* Ciprofloxacin (or another quinolone) 750 mg twice daily *or* Fusidic acid 500 mg thrice daily *or* Linezolid 600 mg twice daily	Fusidic acid 500 mg thrice daily

All treatments are prescribed preferably by means of tablets or capsules. The dosages in this table are the recommended dosages for an adult patient of about 70 kg. Combination therapy will be used because of better effectiveness and a decreased chance of developing resistance

^ɑ^Alternative options should only be used when there is a contraindication (e.g., in vitro resistance, intolerance) for the recommended options

#### Caregivers

In case of treatment failure, a patient’s caregiver (often the patient’s partner) will be asked to participate in the trial to investigate transmission routes from the caregiver to the patient. Presence of a caregiver is not mandatory for the patient’s participation. Caregivers will not be randomized nor treated. Next-generation sequencing (NGS) will be used to determine the type of *S. aureus* strains and to compare them with the strains retrieved from caregivers and/or previous *S. aureus* isolates.

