### Study intervention

Prior to the start of the trial, HPN patients have been screened for *S. aureus* carriage with swabs of the nose, throat, rectum, exit-site catheter, and body regions on indication (e.g. stoma, wound, skin lesion). Subsequently, enrolled patients will visit the regular outpatient clinic appointments every 6 months, in accordance with current guidelines [10].

After randomization, patients will be allocated to one of the following two treatment strategies:*Search and destroy (SD) strategy* focuses on the quick and short, systemic antibiotic eradication of *S. aureus* (Fig. 4)*.* Patients will receive treatment with mupirocin nasal ointment, a chlorhexidine oropharyngeal rinse and body wash, and two systemic antibiotics for one week, according to the Dutch MRSA guideline [10]. Hygienic measures consist of wearing clean clothing every day and frequent change of towels and bed clothes during treatment. Combination therapy is indicated because of improved effectiveness and a decreased chance of developing resistance. After one cycle of treatment, a set of body swabs (nose, throat, rectum, exit-site catheter, and body regions on indication (e.g. stoma, wound, skin lesion) will be taken weekly for 3 weeks to confirm total eradication. In case of persistent *S. aureus* carriage, patients will be treated again. Patients will not receive more than three treatment cycles per round. A successful treatment is defined as three consecutive negative sets of surveillance cultures obtained at least 48 h after completion of treatment and distributed over a period of at least 14 days. Treatment failure is defined when a patient is still a *S. aureus* carrier after three treatment cycles. Relapse of *S. aureus* carriage will be subsequently monitored at the standard new swab rounds, every 3 months. In case of relapse, patients will be treated again as well.*Continuous suppression (CS) strategy* focuses on the continuous, topical eradication o*f S. aureus* (Fig. 5)*.* Whether or not patients are carriers during the year, they will receive mupirocin nasal ointment, an oropharyngeal chlorhexidine rinse, and body wash for extra-nasal body regions every month for 5 days. The same hygienic measures as in the SD strategy group will be applied. Standard swabs of the nose, throat, rectum, exit-site catheter, and other body regions on indication will be taken every 3 months to monitor full body eradication.

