### Outcome measures

*Primary outcome*
Proportion of patients in whom *S. aureus* is totally eradicated during a 1-year time period.Total eradication is defined as 100% of all swabs (nose, throat, rectum, exit-site catheter, and body regions on indication) being negative for *S. aureus* per measured time point.
*Secondary outcomes*
Secondary outcomes are listed in Table 1.

**Table 1 Tab1:** Secondary outcome measures

Secondary outcome measure	Data collection instrument or method
Incidence of *S. aureus* infections	(S)AE forms every 3 months
Overall incidence of infections	(S)AE forms every 3 months
Mortality	Data from electronic patient file
Long-term antimicrobial resistance	Culture results every 6 months and NGS
Number of catheter removals	Data from electronic patient file
Time to first catheter-related infection	(S)AE forms every 3 months and data from electronic patient file
Successful *S. aureus* eradication per body site	Culture results
Relapse rate of *S. aureus* carriage	Culture results and NGS
Transmission routes	Caregivers culture results and NGS
*S. aureus* transmission routes	NGS
Adverse events	(S)AE forms every 3 months
Predictors for infections and treatment failure or success	Binominal regression analysis
Patient compliance	Medication files, counting pills, trial-specific medication diary, modified Morisky Medication adherence questionnaire
Generic health related quality of life	EuroQol 5 dimension, 5 levels questionnaire (EQ5D-5 L)
Treatment satisfaction	TSQM vII questionnaire
Healthcare related costs	iMCQ questionnaire

*iMCQ* iMTA Medical Consumption Questionnaire, *NGS* next-generation sequencing, *(S)AE* (serious) adverse event, *TSQM* Treatment Satisfaction Questionnaire for Medication

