##### Secondary study parameter(s)

Continuous data such as patient characteristics (age, sex, venous access, CRBSIs) will be presented as means ± standard deviation and in case of skewed distributions as medians and range. Dichotomous outcomes will be summarized as percentages (N events/N total). Parameters will be compared between both groups by the Student’s *t*-test, Wilcoxon rank sum test, Chi2-test or Fischer exact test depending on the type of outcome and distribution. A two-tailed *p* value < 0.05 is considered statistically significant. No corrections for multiple tests are applied. Known predictors (such as socio-economic status, pet ownership, location of *S. aureus* carriage, *S. aureus* carriage by caregiver, and active skin disease) for infections and treatment failure/success will be analyzed using a logistic and/or linear regression model.

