## Discussion

This trial will provide guidance for further policy development and implementation of (long-term) *S. aureus* decolonization protocols and other novel infection/transmission preventive strategies. HPN patients, and likely other chronic patient groups such as hemodialysis patients, will benefit from an evidence-based effective and safe long-term *S. aureus* decolonization protocol. Ultimately such a protocol will lower *S. aureus* infections and reduce subsequent hospitalizations, catheter removals, mortality, antimicrobial resistance, and costs.

We believe that with this project we can gain essential knowledge that fills a significant gap in our current understanding of (long-term) *S. aureus* decolonization treatments. As such, the CARRIER trial will prove the efficacy of a long-term *S. aureus* decolonization strategy in HPN patients for the first time. The study will give insight into other important outcome measures such as antimicrobial resistance, *S. aureus* transmission, patient compliance and—as a completely new feature—the role of the caregiver and his/her carrier status.

During the trial, antibiotic drugs will be used according to the national MRSA eradication guidelines [10]. These drugs are also used in clinical practice for eradication of methicillin-sensitive *S. aureus* (MSSA) since there is no separate guideline for MSSA eradication. The MRSA guideline based their advice on studies that were not restricted to the eradication of MRSA only, but included studies evaluating MSSA eradication as well. There is no evidence that any of the treatment options included in the MRSA guideline have a more favorable risk:benefit ratio in the HPN population. Allowance of different treatment regimens that are included in the MRSA guideline enables us to include patients with certain allergies or potential interacting co-medication as well. This is in line with current clinical practice and enables us to include enough patients to answer the research question.

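### Caregivers enter the trial only after the patient's treatment fails, so caregiver carriage cannot be validly assessed as a predictor of treatment failure versus success

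*Protocol article*

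**What the plan says.** - **Sampling rule (Caregivers).** "In case of treatment failure, a patient’s caregiver (often the patient’s partner) will be asked to participate in the trial". The same sentence gives the purpose: the caregiver "will be asked to participate in the trial to investigate transmission routes from the caregiver to the patient". A patient may take part without having a caregiver.
- **Source of caregiver data (Outcome measures, Table 1).** The row on transmission routes gives "Caregivers culture results and NGS", so cultures are taken from the caregivers who join.
- **Analysis (Secondary study parameter(s)).** Caregiver carriage stands in a list of known predictors: "carriage by caregiver, and active skin disease) for infections and treatment failure/success will be analyzed using a logistic and/or linear regression model". Table 1 makes this a secondary outcome: "Predictors for infections and treatment failure or success".
- **Definition of failure (Study intervention, search and destroy strategy).** "Treatment failure is defined when a patient is still a *S. aureus* carrier after three treatment cycles". The text on the continuous suppression (CS) strategy gives no corresponding definition.
- **Prominence (Discussion).** The article presents as new "the role of the caregiver and his/her carrier status".

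Baseline examination and Follow-up describe data from patients only. Bacteriological methods and Quality and safety mention caregivers only as people who are trained to take swabs.

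**The concern.** A regression of failure versus success on caregiver carriage compares carriage among caregivers of patients who failed with carriage among caregivers of patients who succeeded. The sampling rule supplies only the former. The exposure is collected because the outcome occurred, so the comparison group is missing by design and not by chance.

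This is not a detail that can be left to an analysis plan. The article fixes both the sampling rule and the analysis, and the two do not fit together. No later document can recover swabs that were never taken. At stake is one listed predictor in one secondary analysis, on a topic to which the article gives some weight.

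**Working it through.** **1. Planning figure.** Inputs from Sample size and power calculation: 77% eradication in the search and destroy (SD) arm, 55% in the CS arm, power 80%, alpha 5% (taken as two-sided), 1:1 allocation. With unpooled variance:

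n per arm = (1.960 + 0.842)² × (0.55 × 0.45 + 0.77 × 0.23) / 0.22² = 68.86, so 69 per arm and 138 in total.

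This reproduces the article's figure, which is not in dispute. It is used below only to size the groups.

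**2. Expected failures and successes, as a proxy.** The complements of the 1-year eradication rates stand in for treatment failure:

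- SD failures: 0.23 × 69 = 15.87
- CS failures: 0.45 × 69 = 31.05
- All failures: 46.92, about 47 (34% of 138)
- Successes: 138 − 46.92 = 91.08, about 91 (66%)

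Under the proxy, caregiver status could be known for about 47 patients, or fewer because some have no caregiver. It would be known for none of the 91 successes.

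**3. If failure means the same in both sections.** Every patient with a known caregiver status is a failure. The outcome is constant and a complete-case model gives no odds ratio (OR).

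The OR depends on the unobserved carriage proportion r among caregivers of successes. With q the proportion among caregivers of failures, OR = [q/(1 − q)] / [r/(1 − r)]. The documents give neither q nor r, so these values are assumptions:

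| q | r = 10% | r = 30% | r = 50% |
|---|---|---|---|
| 30% | 3.86 | 1.00 | 0.43 |
| 50% | 9.00 | 2.33 | 1.00 |

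The same failure data fit a strong positive association, none, or (for q = 30%) an inverse one. Standard imputation cannot supply r, because no success has an observed value.

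**4. If failure differs.** Suppose the trigger is carriage after three cycles and the model's outcome is the 1-year result. Some patients could fail a round, have a caregiver sampled, and later count as a success. An OR could then be computed, but only among patients who had already failed once. Patients who never failed remain absent, so the estimate is selected on an event closely tied to the outcome.

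**5. What sampling at inclusion would buy.** Assume 30% carriage among caregivers of successes and a two-sided 5% test of two proportions:

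| OR | Every patient has a caregiver (47 vs 91) | Half have one (about 23 vs 46) |
|---|---|---|
| 1.91 | 42% | 24% |
| 2.33 | 64% | 37% |
| 2.85 | 82% | 53% |
| 3.50 | 93% | 68% |

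The effect would become estimable, but power would be modest unless it is large.

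**The case against.** The strongest objection is that the trigger and the modelled outcome may be different events. The three-cycle rule applies within a treatment round, patients are treated again on relapse, and the predictor analysis does not say which failure it means. This stands. It rules out saying that no OR could exist under any reading, and it makes the counts above a proxy. It does not rescue the analysis, because patients who never fail still have no caregiver data.

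A reader might infer more, in four ways that the documents do not support:

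- **That CS caregivers are never sampled, leaving at most about 16 from the SD arm.** The CS flow chart and the schedule figure are not shown, and the schedule's footnote on eradication failure is not limited to one arm. The 16 is also an expected count from a 1-year rate, not a ceiling on three-cycle failures. All that can be said is that the visible text defines treatment failure only for SD.
- **That the caregiver aim as a whole fails.** Strain comparison among failures remains feasible. Sampling after failure does leave direction uncertain. But the article also plans comparison with the patient's earlier isolates and stores isolates, which gives some information on direction, though not proof.
- **That the model would produce an infinite OR.** This would require coding unsampled caregivers as non-carriers, and nothing in the article proposes that.
- **That caregiver carriage is useless for every outcome.** The predictor list also covers infections. An association with infection can be computed among failures, but it is conditional on failure and likely to be sparse, since the article expects few infections.

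**Conclusion.** The point holds in limited form. The sampling rule and the failure/success predictor analysis contradict each other, and the association cannot be validly estimated under either reading of failure.

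The rough size is 91 of 138 patients (66%) without the exposure, all of them successes. This assumes that the planning rates are met and that 1-year non-eradication approximates the trigger. It also counts every success as a lost observation, although some would have no caregiver to sample; the article does not give that share. The conclusion does not depend on the exact count.

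The problem affects one predictor in a secondary analysis. The primary comparison of the two strategies is unaffected, and descriptive caregiver-patient strain comparison can go ahead.

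**What to change.** **Wording only:**

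1. Under Secondary study parameter(s), remove caregiver carriage from the predictors of treatment failure/success.
2. State that caregiver-patient strain concordance, including comparison with the patient's earlier isolates, will be reported descriptively among failures.
3. Label any association between caregiver carriage and infection as conditional on failure.
4. State which definition of failure triggers the approach to caregivers in each arm, and whether the predictor analysis uses the same one.

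These changes need no new data.

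**If the sponsor wants to keep the predictor:** collect caregiver status at the patient's inclusion, whatever the later outcome, and use that value in the model. This costs up to 138 additional caregiver swab sets and consents. Trial status says recruitment began at the end of 2017, so inclusion values could be collected only for patients not yet enrolled. The power table above shows what even full collection could be expected to detect.

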#### Bacteriological methods

##### Identification of *S. aureus* and storage of positive cultures

To screen patients for *S. aureus* carriage, flocked swabs with moisture (Eswab) will be used. To ensure high quality of this procedure, training for the nurses and patients’ caregivers and an instruction brochure will be provided prior to the start of the study. After collection, the swab will be placed in 100 μl of saline and centrifuged. Real-time PCR (polymerase chain reaction) and conventional cultures will be used for the detection of *S. aureus* isolates. Cultures will be performed after broth enrichment, which improves the performance of chromogenic solid media for the detection of *S. aureus* in clinical samples (sensitivity of 95–97%). This is according to the national MRSA detection guidelines and will be the same for all the participating centers [11]. For perineum swabs, CAN agar plates will be used. This is a selective microbiological medium for *S. aureus*, which inhibits Gram-negative bacteria during culture. All *S. aureus* isolates will be stored at − 80 °C in glycerol-containing liquid media for the duration of 1 year after the end of the study.

##### Next-generation sequencing

NGS, performed with Illumina NextSeq (Illumina, San Diego, CA, USA), will be used in a subgroup of subjects (for example, in case of relapse or occurrence of active *S. aureus* infection). *S. aureus* strains will be distinguished by comparing single nucleotide polymorphisms (SNPs) in the core genome and by relating these SNPs to the genealogical tree of *S. aureus*. A cut-off point of 30 different SNPs will be used to classify *S. aureus* strains as distinct [12].

#### Follow-up

Patients will be followed for 1 year. At months 6 and 12, swabs will be obtained at the outpatient clinic and questionnaires regarding adverse events (AEs) will be collected. In between outpatient visits, at 3 and 9 months, swabs will be sent to the laboratory and patients will be interviewed via telephone to assess adverse events and treatment satisfaction with a validated questionnaire (TSQM vII). At inclusion and 6 and 12 months, generic health-related quality of life and health care costs will be measured with questionnaires as well (EQ-5D-5 L, iMCQ). Discontinuation of study treatment by patients will be recorded, including the reason for discontinuation. If possible, a final visit procedure (collecting swabs 1 year after inclusion) will be performed.

#### Patient compliance

At months 6 and 12, patient compliance will be monitored by medication files, a trial-specific medication diary (on paper or digital via medication application MedApp), and specific questions regarding medication adherence. In addition, all patients will have a study-specific list with information about their *S. aureus* screening and treatment protocol. We chose this method for measuring adherence because it is pragmatic and reliable, without influencing the daily practice too much.

#### Data management

All data will be handled confidentially and, where necessary, anonymized. The investigator will record all data in an eCRF. All files will be encrypted by a password only known by the investigators. Originals of laboratory or other tests related to the study will be kept on file at the study site. This study will be performed in accordance with the legal laws formulated in the Dutch “Wet Bescherming Persoonsgegevens”.

### Analysis

#### Sample size and power calculation

Hardly any literature is available regarding long-term efficacy of the CS group on total *S. aureus* carriage eradication. Even when articles describe similar eradication strategies as the CS group, endpoints vary from only local, nasal *S. aureus* eradication to *S. aureus* infections. Consequently, total body site (de)colonization has not been described thoroughly. Based on a few studies with quite similar eradication strategies, it is, however, possible to make an assumption about the long-term efficacy [10, 13–16]. The eradication rate of the SD strategy group is expected to be 77% and for the CS strategy group 55% over 1 year. Based on the settings binary outcome (carriage yes/no), superiority trial, power (1 − β) of 80% and a significance level (α) of 5%, a total of 138 patients (2 × 69) are required to detect a significant increase from 55 to 77%.

